***Vita Mamba* School Feeding Project**

**Study Protocol**

**Abstract**

This study builds on the *Mamba Lespri* School Feeding Project, conducted in Cap-Haitien, 2012-2013, to improve the nutrition of school-aged children, now in a rural context. Our main objective is to test the effect of a locally produced food, Vita Mamba, on reducing anemia and improving growth in school-aged children. The study uses a longitudinal randomized cluster design with three schools assigned to two groups : Group 1: Control (deworming), Group 2: Vita Mamba (and deworming). Schools will be matched on socio-economic, demographic, and nutritional characteristics and randomly assigned to one of the two comparison groups. Approximately 400 Haitian school children ages 3-16 years of age and their parents will be recruited and enrolled to be followed during the 2014-2015 school year. Data will be collected from two groups of participants at each school: children and parents. At baseline, socio-economic and demographic information will be collected from parents. Children will then be followed at two time points: at the beginning (baseline) and end (endline) of the study for nutrition measures (weight and height, and hemoglobin concentration). Parents will be surveyed for socio-economic characteristics, child diet and health, and anthropometry.

**Background and Significance.** The Haitian Ministry of Education has identified poor nutrition as a problem among Haitian school children. Poor nutrition stunts growth and development and compromises the immune system, leaving the body more vulnerable to disease. In Haiti, 20.9% of children less than five years are stunted and 11.4% are underweight (MSPP, 2013), but information about the nutritional status of the school-aged population is limited. One study of Haitian children between the ages of 11 and 19 years showed two-fifths were stunted (Psoter, et al, 2008).

The diets of school-aged children are likely deficient in vitamin A, iron, iodine, zinc, and potentially other micronutrients, similar to younger children in Haiti (Best, et al, 2010). Among 4-5 year olds, 35% were found to be vitamin A deficient and almost half were anemic (WHO, 2007), which can affect cognitive development, memory, and other mental function (NIH, 2011). Iodine deficiency, which has been associated with lower IQ scores, affects 59% of the entire Haitian population (MSPP, 2005). The exact prevalence of zinc deficiency in Haiti is unknown as is the case for most countries given the difficulties in measuring zinc nutrition though diarrhea prevalence, which is associated with zinc deficiency, is high in Haiti (MSPP, 2007). Intestinal parasites closely linked to nutrient deficiencies infect about a third of all Haitian school-aged children (WFP, 2010). Inadequate calories, protein and micronutrients stunt growth and intellectual development and compromise the immune system, leaving the body more vulnerable to disease (WHO, 2000).

In Haiti, despite the numerous and longstanding school feeding projects, there is limited information about the health and educational outcomes of these programs. Few programs have conducted evaluations designed to demonstrate impact or even program performance.  This study is designed to first characterize the nutritional situation of school-age children, and second, evaluate the effectiveness of a Ready-to-Use Supplementary Food (RUSF), Vita Mamba, for nutrition, health, and educational outcomes. It is among the first globally to examine a lipid-based RUSF in school-age children. The project will be implemented in the north of Haiti, in the Terrier Rouge zone. Vita Mamba will be introduced as a snack targeting children 3-12 years of age within a school feeding program.

**Study Aims:** To evaluate the nutrition impacts, especially growth and reduction of anemia, associated with the local product (Vita Mamba) offered through school feeding programs.

**Methodology**

**Study Design**. A quasi-experimental evaluation design is planned for this project.  Three primary schools will be matched on socio-economic and demographic factors and randomized into two participant groups:

*Group 1* (Control): Children 3-16 years of age in a school that does not normally participate in a school feeding program and will receive no food-based intervention during the study period. Deworming with Albendazole administered.

*Group* *2* (Vita Mamba): Children 3-16 years old in a school that does not normally participate in a school feeding program and who will receive Vita Mamba during the study period. Deworming with Albendazole administered.

**Study Activities**. This project will take place in schools in a communal section of the Terrier Rouge zone. This is a quasi-experimental study that will be coordinated by Washington University in St. Louis (WUSTL) in partnership with Meds & Food for Kids (MFK), Haiti’s National School Lunch Program (le Programme National de Cantine Scolaire, PNCS) and the Ministry of Public Health and Population (MSPP). There are three phases of the project: 1) planning, 2) intervention and 3) reporting and dissemination of findings.

Planning & Recruitment Phase. In the planning phase, there will be three primary activities: recruitment of staff and participants; training the study team; and program organization.

The Study Coordinator will be hired and begin work in September 2014. Two enumerators will be hired in October 2014. With the Principal Investigator, the coordinator will recruit and train the enumerators during the planning phase. The Study Coordinator will work with school personnel to enroll families of schoolchildren aged 3 to 16 years.

Parents/caregivers of eligible students will be acquainted with the study methods and procedures and will be asked to sign an informed consent form, which will be presented in the local languages (French and Creole). If parents/caregivers are unable to read, the consent form will be reviewed in full by French and Creole speaking trained enumerators to ascertain that the parent/caregiver has understood the nature of the study and is voluntarily enrolling their child in the study. A simple script will be reviewed with the students participating in the study to explain the RUSF product and the purpose of the anthropometric measurements and acceptability study.

Before the launch of the pilot study, WUSTL will form the study team, which will review and complete the necessary IRB certification program appropriate for this project. The training will include three (3) components: 1) Technical information and survey administration; 2) protocol instruction for anthropometric and hemoglobin concentration measure; and 3) field testing and validation exercises. The team of enumerators will receive detailed information regarding the product’s ingredients, functionality, and recommended consumption rates. Additional training will be provided to the team to explain the consent process as well as data collection and communication methodologies. Instructions will be given to the team on the correct methodology for conducting the acceptability study.

Intervention Phase.

**Sample Schools and Participants.** The intervention phase of the project will take place during the academic year from September 2014 through June 2015. Selection of the three schools in a communal section of the Great Basin region (Northeast Department) will be based on student socio-economic and demographic information, school size, and current school feeding program. All schools and students have an equitable chance of being included in the study. Three (3) schools will then be matched on important characteristics (basic anthropometry, SES, and school size) and will be assigned to one of two study groups described above: Group 1: Control (Danda); Group 2: Vita Mamba (Dolval).

At each of the three schools, two groups of participants will be part of the study: parents and children. A full description of the study will be provided and they will be invited to participate through the informed consent process. Parents and other caregivers of potentially eligible children will also be contacted at the beginning of the school year. They will be provided with a description of the study and invited to attend one of several meetings at the school with their children. At the meeting, the Study Coordinator will review and provide a full description of the study.

Children of interested parents/caregivers will be screened for eligibility based on the following criteria:

• Children 3-16 years old ;

• Children in good health [no fever, no congenital health condition];

• Children not severely malnourished [weight-for-height Z score >-2];

• Enrollment in the study school for the academic year 2014-2015.

Exclusion criteria are the following:

• Allergy to peanuts or soy;

• Fever or congenital or major health condition affecting the child;

• Child severely malnourished (weight-for-height Z score <-2).

Once eligibility is established, parents/caregivers will go through the informed consent process individually. The study staff will provide the children with a verbal description of the study, which will explain the purpose of the study, their role in the study and what to expect during the data collection methods. The children will be asked to give verbal assent. Following this, parents will be asked to return to the school on a scheduled date and the baseline survey will be administered.

**Sample size.** Power calculations were used to determine the adequacy of sample size, predetermined by total number of eligible children in the study schools and study budget. Using an estimate of difference-in-difference, mean change in Hb of 0.40 (SD 1.2) based on previous studies, adequate sample size need was estimated to be 143 per group [alpha=0.05 and power (1-β=0.80)] (Nga T. et al. 2009). With a design effect of 1.06 applied and an estimated 10% losses to follow-up, the study was found to be adequately powered to detect the hypothesized difference in Hb with 321 children enrolled (Wittes et al. 2002).

**Intervention & Methods.** Students in Group 2 will receive the RUSF/Vita Mamba snack daily for one academic year, 2014-2015. Each RUSF sachet (50g) contains 260 kcal and 100% RDA for most micronutrients. Simple messages about the importance of the RUSF, nutrition, and hygiene will be communicated at a low intensity level in group 2. All children will receive deworming, Albendazole, according to the national protocol of MSPP. Two types of surveys will be developed and administered for data collection in this study.

*Child measures and survey:* Students will be followed longitudinally during the school year on a range of health, nutrition, and education outcomes. A baseline, midline, and endline survey will be administered to assess nutrition and education impacts as well as acceptability of the product, Vita Mamba, to students as part of a school feeding program.

Hemoglobin concentrations in the students will be determined using the Hemocue system, which measures red blood cell status and is reported in grams per 100 milliliters (g/dl). A droplet of blood will be collected in a sterile fashion with a fingerstick and a microcuvette in one continuous process. The results will be compared to WHO anemia Hemoglobin cut-offs for children 5 - 11 years of age (WHO, 2011). The Seca Model 874 (Digital) 440 lb x 0.1 lb resolution and the ShorrBoard measuring board will be used to collect weight and height measures. These measures will be used to determine body mass index (BMI), anthropometric z-scores, and the prevalence of stunting, underweight and wasting, which will be compared to WHO Growth Standards.

*Parental survey:* At baseline and endline, a survey will be administered at the school to parents of children in the study. At baseline, after informed consent procedures, socio-economic and demographic information will be collected, including parental education, age, occupation, family size, income/assets, household water and sanitation services, health and nutrition behaviors, and access to healthcare. This will allow the evaluation team to control for confounding factors and stratify analyses. Further, additional recall data on frequency of consumption, dietary diversity, and morbidities of participating children will be collected from parents at both baseline and endline time points. Finally, height and weight measures will be taken on the parents.

Reporting & Dissemination Phase. During this phase, data will be analyzed and reports written based on the results of the study. Presentations will be made to donors, MSPP, PNCS, MFK, and the community with the results and next steps. Other dissemination activities could include writing policy and programming briefs and journal articles, and presenting at national and international conferences.

**Innovations and Impacts.** This is the first study to examine the effectiveness of a Ready-to-Use Supplementary Food (RUSF) with deworming in a rural Haitian context for addressing poor nutrition. If there are positive findings, the results may be used to increase and advance the school feeding programs in Haiti. Further, there is potential to affect policy and programming at the national level with regards to child nutrition in Haiti. At the international level, this study will contribute to the evidence base for supplementary foods as part of a school feeding protocol.

**Sources of Support**. This project is funded by the United States Department of Agriculture (USDA) Foreign Agricultural Service Micronutrient Fortified Food Aid Products program FFE-521-2012/034-00.

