The direct benefits to the child will be decreased likelihood of nutrient deficiencies and improved health. Interventions that target prepubescent children have been shown to decrease the prevalence of nutritional deficiencies and improve school performance and overall child health (Soemantri, Pollitt, & Kim, 1985; Grantham-McGregor & Ani, 2001). Access to high quality, nutritious foods during the school day can boost enrollment, improve cognitive development, and increase performance measures on school exams (Soemantri, Pollitt, & Kim, 1985; Grantham-McGregor & Ani, 2001; Seshadri & Gopaldas, 1989). School feeding programs have also been shown to increase memory and the speed of processing by alleviating short-term hunger (Simeon & Grantham-McGregor, 1989).

The results of the study will demonstrate the effectiveness of using a lipid-based Ready-to-Use Supplementary Food (RUSF) as part of a school feeding program. While school feeding programs have been studied around the world, this study is among the first to examine a lipid-based RUSF in school-age children. It is intended to treat poor nutrition among school-age children on a population level with the possibility of long-term positive health and economic outcomes for the community. School feeding and increased enrollment have a positive influence on the economy and public health, which can be passed onto the next generation. The Government of Haiti is directly involved in this study and intends to use the results for future policy and programming in the country.

The new study in a rural area with the modifications described also allows the investigation of interventions to prevent anemia and promote growth with local products. The new study also allows us to test the RUSF against a strategy based on food.

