Appendix B: Privacy and Confidentiality

Privacy

- During the recruitment process, the study team will visit with individuals at the time of school enrollment in a secure place at the school.
- During the consent process, the study team and participants will sit in a secure place such as an empty classroom at the school to ensure that they are appropriately distanced from others for privacy purposes.
- Each child will be measured at a reasonable distance away from the other children to ensure the privacy of the children. The three schools, which will be placed into one of two groups, have been selected so as to prevent contamination between the groups.
- Information collected will pertain to the well-being of the child as relates to the Vita Mamba, the food product. Any information beyond the scope of program evaluation and its acceptance will not be obtained.

Data Collection

- Paper/hard copy records (hard copy surveys, questionnaires, case report forms, pictures, etc.) – Surveys will be stored in a locked box at the Washington University work space in Haiti - Breda, Cap Haitien.
- Electronic records (computer files, electronic databases, etc.) - Only two computer hard drives will contain the names of participants. These computers will also be locked and secured in the Washington University work space in Haiti, Breda, Cap Haitien. Data files will be transferred periodically by jump drive back to the Brown School of Social Work to the computer hard drive of the PI of this study.
- The study team will use the Hemocue system for measuring hemoglobin samples. The disposable microcuvette, which is used to prick the child’s finger, collects a small amount of blood and then mixes it with the reagents immediately. The study team will then place the microcuvette into the portable analyzer, which will report the results on the display. After use, the microcuvettes will be placed in a standard, medical waste container and disposed of properly at the local health center.

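### Eligibility rests on undated enrollment for 2014-2015, and nothing says when families learn which school gets the food, so children drawn by the food can enter Group 2 only

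*Protocol*

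**What the plan says.** All references are to the Protocol.

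- **Allocation.** Methodology, Sample Schools and Participants, says that the three matched schools "will be assigned to one of two study groups described above: Group 1: Control (Danda); Group 2: Vita Mamba (Dolval". The groups are thus tied to named schools in the text.
- **Recruitment.** The same section then says: "Parents and other caregivers of potentially eligible children will also be contacted at the beginning of the school year". Families are invited to school meetings, and "At the meeting, the Study Coordinator will review and provide a full description of the study". Next, "Children of interested parents/caregivers will be screened for eligibility based on the following criteria". Individual consent follows, and then the baseline survey.
- **Place and time.** Appendix B (Privacy) says that during recruitment "the study team will visit with individuals at the time of school enrollment in a secure place at the school".
- **School criterion.** The only one is "Enrollment in the study school for the academic year 2014-2015". It carries no date.
- **Effect of food on enrollment.** Appendix A (Benefits) states: "Access to high quality, nutritious foods during the school day can boost enrollment".
- **Safeguards.** The sample size is framed as a difference-in-difference. A baseline parental survey covers socio-economic and household factors, and "This will allow the evaluation team to control for confounding factors and stratify analyses". Appendix C adds multivariate regression and, only if needed, propensity score matching. Appendix B says that the schools were chosen to avoid contamination between groups.

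**The concern.** When whole schools are allocated and individuals are recruited within them, the allocation can influence who is recruited. Here the school criterion can be met by enrolling once the allocation is known, recruitment takes place at enrollment, and the protocol itself names school food as something that raises enrollment. According to the Study Design section, these schools do not normally have a feeding program, so the food would be a new attraction, offered in Group 2 only.

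Children who come for the food may differ from the regular pupils in hunger, household means, parental motivation or hemoglobin. If their expected change over the school year also differs, part of the between-group difference in hemoglobin or growth would reflect who was enrolled and not Vita Mamba. A larger sample does not shrink a bias of this kind.

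**Working it through.** **1. Sequence.** The text supports part of the chain and leaves part open.

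| Step | What the protocol gives |
|---|---|
| Schools tied to groups | Yes, by name, and described before the contact with parents |
| Date of assignment | Not given |
| When families learn their own school's group | Not given; a full study description precedes screening and consent, and no step withholds the allocation |
| Roll date for eligibility | Not given |
| Limit on, or record of, new enrollments or transfers | Not given |
| Recruitment at school enrollment | Yes, Appendix B |

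The order of assignment and recruitment is an inference. The school-selection paragraph puts assignment before contact with parents, but the Planning & Recruitment Phase, described earlier in the protocol, already includes recruitment of participants. On either reading, no rule keeps out a child who enrolls because of the food.

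**2. What the safeguards cover.**

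- *Difference-in-difference* removes a fixed difference in level between groups. It does not remove a difference in expected change. If more anemic children are drawn in, regression to the mean alone can raise the Group 2 change.
- *Regression adjustment and propensity matching* address measured factors such as income and assets, parental education, water and sanitation, diet and morbidity. The reason for joining the school is not among the listed survey items.
- *Choosing schools to avoid contamination* may limit movement between study schools. It does not address children newly enrolled from elsewhere.

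**3. The plan's own figure.** Inputs from the Sample size section: difference 0.40, SD 1.2, alpha 0.05 (two-sided assumed), power 0.80.

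n per group = 2 × [1.2 × (1.960 + 0.842) / 0.40]² = 141.3, so 142. The t-based calculation gives 143, which is the stated figure. The point raised here changes no sample size.

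**4. Precision as planned.** Take 321 enrolled, 10% loss, design effect 1.06 and equal groups (an assumption):

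- effective n per group = 321 × 0.9 / 1.06 / 2 = 136.3
- SE = 1.2 × √(2 / 136.3) = 0.145 g/dl

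**5. Illustrative bias.** Let f be the share of Group 2 drawn in by the food and d the difference between their expected hemoglobin change and that of the other Group 2 children. Then bias = f × d. Neither f nor d is in the protocol. The error rate is the chance of a significant result with no true effect, 1 − Φ(1.96 − bias/SE) + Φ(−1.96 − bias/SE).

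| f | d (g/dl) | Bias (g/dl) | Share of 0.40 | Bias / SE | Two-sided error rate (nominal 5%) |
|---|---|---|---|---|---|
| 5% | 0.3 | 0.015 | 4% | 0.10 | 5.1% |
| 20% | 0.5 | 0.10 | 25% | 0.69 | 10.6% |
| 10% | 0.4 | 0.04 | 10% | 0.28 | 5.9% |
| 30% | 0.8 | 0.24 | 60% | 1.65 | 37.9% |

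The spread from 4% to 60% shows how strongly the answer depends on the assumptions. A d of 0.4 already equals the whole hypothesized effect, so the last row is an extreme case.

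**The case against.** The strongest reply has four parts.

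- **Missing links.** For the food to draw children in, a family must learn which school gets it, enroll a child there, and do so before screening. No public announcement is described. A reader might infer that control families decide on consent knowing that they will get no food. The protocol does not say so: it promises a full description of the study, not disclosure of the school's own group. Likewise, it gives no assignment date, so it is not established that assignment precedes all recruitment. Both points stand, and the concern is limited to what the plan leaves possible.
- **A pool known in advance.** The sample size is said to be set in part by the number of eligible children in the study schools, which suggests a known population. But that is not a dated cut-off and excludes no later joiner.
- **The enrollment statement is general.** It summarizes literature on school feeding and does not predict a shift at these schools in one intake. This is fair. It shows that the mechanism is one the protocol accepts, not that it will operate here.
- **Measured differences are handled.** Poorer families would be identified by the baseline survey, and hunger partly by the diet data. This stands and narrows the concern to unmeasured differences in expected change and any regression to the mean left after adjustment.

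**Conclusion.** The point holds as a risk that the eligibility rule leaves open. As written, a child who joins the Vita Mamba school because of the food qualifies for Group 2, and the planned analyses can remove only part of any resulting difference. The documents do not show that such enrollment occurred, that families knew their group before consent, or which way a bias would run.

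The size is unknown. The figures of 0.015-0.10 g/dl (4-25% of the planned effect), or up to 0.24 g/dl on wider assumptions, are illustrations on inputs that the protocol does not supply. They also make no allowance for the planned covariate adjustment. The case for a change rests on the gap in the rule and the low cost of closing it. It is a recommended improvement, not a fatal flaw, in a study that describes itself as quasi-experimental.

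**What to change.** In all three schools, limit the analyzed population to children on the school roll on a stated date before the allocation is made known to families, and state when and how families are told. Later joiners may receive the food but are left out of the primary analysis.

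Where this does not delay the feeding, complete consent and baseline measurement before families learn their group. That condition matters. The coordinator starts in September 2014 and the enumerators are hired in October 2014, while the intervention phase runs from September 2014, so holding the allocation back until every baseline is complete could push the feeding into the school year.

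The roll-date rule costs one eligibility sentence and the loss of a few late-joining pupils from the analysis. It leaves the sample size formula unchanged. It does not by itself prevent different consent rates between schools; counts of eligible, consenting and refusing children per school would show these, and are a matter of reporting.

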Appendix C: Analysis

The primary outcomes tested by the study will be height, weight, and hemoglobin levels of the child, as markers of growth and micronutrient nutrition. The secondary outcomes include: nutrition (weight, diet, and dietary intake); health (morbidities such as diarrhea, and fever). Finally, the study will be examining the feasibility and acceptability of using Vita Mamba in the school feeding context and thus looking at ease of delivery.

The analysis methods will include descriptive and experimental data procedures. Several univariate analyses and multivariate regression analyses will be run to model outcomes and adjust for potential confounding factors. As a longitudinal study, the study will run panel regression by generalized least squared with random effects. Interaction terms will be introduced. As necessary, propensity score matching will be introduced to ensure the two groups are comparable.

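### Enrolment is cut at weight-for-height Z of -2, so a wasting prevalence on that index and cut is 0% at baseline by construction

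*Protocol*

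**What the plan says.** Eligibility is set in the Protocol, Methodology, under Sample Schools and Participants. The inclusion list has "Children not severely malnourished [weight-for-height Z score >-2" and "Children 3-16 years old". The exclusion list has "Child severely malnourished (weight-for-height Z score <-2". Informed consent follows once eligibility has been established.

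Two other places rely on describing nutritional status:

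- Background and Significance: "This study is designed to first characterize the nutritional situation of school-age children". Evaluating the product comes second.
- Child measures and survey: "These measures will be used to determine body mass index (BMI), anthropometric z-scores", together with "the prevalence of stunting, underweight and wasting, which will be compared to WHO Growth Standards". No index or cut-off is given for wasting.

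Two places limit how much hangs on this. The Study Aims read "To evaluate the nutrition impacts, especially growth and reduction of anemia", with no mention of description. Appendix C states "The primary outcomes tested by the study will be height, weight, and hemoglobin levels of the child", and wasting is in neither its primary nor its secondary list.

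**The concern.** A prevalence cannot be estimated in a sample from which the cases have been removed. If wasting is judged on the index used for eligibility and at the same value, the baseline figure is fixed before any child is enrolled and says nothing about the schools. The protocol makes no provision for reporting on the children screened out.

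Two consequences follow. A reader could take a baseline wasting figure of zero as a finding about rural Haitian schoolchildren, a group for which the protocol itself says information is limited. And because the figure starts at zero, it can only stay there or rise. Some rise is expected without any change in the population, because children just above the cut at baseline will sometimes measure below it later.

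**Working it through.** **Inputs.** From the Protocol: enrolment requires weight-for-height Z above -2, and children below -2 are excluded. The protocol gives no Z distribution, no share excluded and no definition of wasting, so there is no stated figure to reproduce. Its one design calculation (143 per group for hemoglobin) does not enter here.

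**Assumptions.** Wasting means Z below -2. In the screened population Z is normal with SD 1 and mean m = 0, -0.5 or -1. Baseline and endline Z have correlation r = 0.7 or 0.9, with the same mean and SD at both times and no treatment effect.

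**Step 1, baseline prevalence among the enrolled.** P(Z < -2 given Z > -2) = 0. This needs only the definition of wasting, not the distribution.

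**Step 2, share removed.** With Φ the standard normal distribution function and φ its density, the share is p = Φ(-2 - m). This gives Φ(-2) = 0.0228, Φ(-1.5) = 0.0668 and Φ(-1) = 0.1587.

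**Step 3, shift in mean Z among the enrolled.** φ(-2 - m) / (1 - p) gives 0.055, 0.139 and 0.288.

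**Step 4, endline prevalence among the enrolled with no effect.** Let b be the probability that both the baseline and endline values lie below -2 (bivariate normal, correlation r). The prevalence is (p - b) / (1 - p).

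| Assumed mean Z | Screened children removed | Baseline wasting, enrolled | Endline wasting, r = 0.9 | Endline wasting, r = 0.7 |
|---|---|---|---|---|
| 0 | 2.3% | 0% | 0.96% | 1.57% |
| -0.5 | 6.7% | 0% | 2.45% | 4.14% |
| -1 | 15.9% | 0% | 5.13% | 8.88% |

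**Step 5, does the rise cancel between groups?** It does if the groups have the same baseline distribution. If one group has mean -0.5 and the other -1, the spurious endline difference is 5.13 - 2.45 = 2.68 points (r = 0.9) or 8.88 - 4.14 = 4.74 points (r = 0.7). With means -0.5 and -0.7, the same formula gives 3.37% and 5.75% for the second group, so the difference is 0.92 or 1.61 points.

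**Step 6, other indices.** At a given height, a child with low weight-for-height is a lighter child, so removing such children is likely to lower the underweight prevalence. The size cannot be worked out from the protocol. Stunting depends on height, which this rule does not cut directly, so no direction of bias in stunting is claimed.

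**The case against.** The strongest reply is that little of the study depends on wasting. Description is absent from the Study Aims, and wasting is in neither outcome list of Appendix C. Hemoglobin, height, diet and morbidity are still measured in the enrolled children. The same cut applies to both groups, and the sample size is framed as a difference-in-difference, so drift after selection mainly harms a before-after reading within one group. All of this stands, and it limits the point to a descriptive measure. It does not remove it: the protocol still states description as the first purpose and still plans the wasting figure. The cancellation between groups also depends on similar baseline distributions. Matching on basic anthropometry helps, but with three schools it does not guarantee that.

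It can also be said that defining wasting belongs in a statistical analysis plan. That is fair, and the missing definition is not itself the point. If the plan uses a different index, such as one based on BMI, the exact 0% no longer follows, although the thinnest children by weight-for-height are still absent.

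A reader might infer more than the documents support:

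- That weight-for-height does not fit most children aged 3 to 16. The protocol gives no age or height limit for the index, so this would rest on outside knowledge. It also pulls the other way: where the index could not be computed, the exclusion could not be applied.
- That the study's aim is defeated. One descriptive purpose is limited; the stated aim is not.
- That biased prevalence figures would feed national policy. The protocol ties policy use to the product's effectiveness, not to baseline prevalence.

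**Conclusion.** The eligibility rule and the plan to report wasting conflict and must be reconciled. If wasting is weight-for-height Z below -2, its baseline prevalence among enrolled children is exactly 0% by design, underweight is probably understated, and a later rise in wasting is partly an artefact. Under the stated assumptions the artefact is about 1% to 9% of enrolled children at endline, and the rule removes 2.3% to 15.9% of those screened. These ranges are illustrations, because the protocol gives no Z distribution or correlation; only the 0% is free of them.

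The comparison of height, weight and hemoglobin between groups is not invalidated by the cut. The consequence is a wrong descriptive result, together with a change in wasting that should not be read as an effect.

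**What to change.** - Report baseline wasting, underweight and stunting for all children measured at screening, before exclusions, with the number excluded by this rule in each school.
- Take consent before those measurements, so that the data on excluded children may be used.
- State that prevalence among enrolled children is not a population estimate.
- Do not read the change in wasting prevalence from baseline to endline as an effect. Compare the continuous z-score between groups instead, with the baseline z-score in the model, since selection acts on that value.
- State the index and cut-off used for wasting, so that its relation to the eligibility rule is visible.

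The cost is small. Weight and height must be measured anyway to apply the rule, so the work is to keep and report the screening data. The one real change is that consent moves a step earlier and is sought from some families whose children will not be enrolled. No change to the eligibility threshold or index is proposed.
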